## Abstract

**Introduction:**

Patients recovering from long COVID often endure a spectrum of neuropsychiatric symptoms, including cognitive impairment, memory deficits, mood disturbances and sleep disorders, that significantly impact their quality of life. Acupuncture, particularly electroacupuncture, has shown promise in addressing these symptoms. Currently there is no high-quality clinical trial for acupuncture on long COVID neuropsychiatric symptoms.

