**Methods and analysis:**

In this 24 weeks, sham-controlled, patient-assessor-blinded randomized trial, 150 long COVID patients will be equally allocated to either an electroacupuncture group (EAG) or a sham control group (SCG). Each subject will receive a total of 32 intervention sessions over a 16 weeks intervention phase (two sessions each week) and will be followed up for an additional 8 weeks. Primary outcomes include changes in the Mini-Mental State Examination (MMSE) and the Chinese version of the Beck Depression Inventory (CBDI) scores. Secondary outcomes include the Insomnia Severity Index (ISI), Brief Fatigue Inventory-Taiwan (BFI-T), and the Short Form 12 (SF-12). All outcomes will be assessed at baseline and then at 4 weeks intervals during both the treatment and post-treatment periods.

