### Sample size

The target sample size was determined by reviewing prior trials using MMSE and BDI to assess the effectiveness of acupuncture versus sham treatment. The observed differences in MMSE and BDI scores between groups were 2.82 and 3.96 points, respectively (39, 40). Based on effect sizes of 0.76 for MMSE and 0.75 for BDI, the BDI-based between-group difference was smaller and was therefore selected for estimation of sample size to yield a more conservative result. To control the overall type I error and ensure sufficient statistical power, the following parameters were applied: a two-sided α level of 0.025 (Bonferroni correction), a power of 0.8, and an equal allocation ratio (1:1) between the acupuncture and sham acupuncture groups. Under these assumptions, the calculation yielded a requirement of 36 subjects per arm. Allowing for an anticipated 20% dropout rate, the target total sample size was adjusted to 90 cases. To increase robustness and ensure an adequate sample reserve for future subgroup analyses, we plan to recruit 150 participants (41–44). Sample size estimation was conducted using G*Power (Version 3.1).

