### Data processing and analysis

Descriptive metrics, namely recruitment rates, attrition rates, and treatment adherence, will be reported as count and percentage. All efficacy and safety endpoints will be analyzed under a modified intention-to-treat (ITT) framework. Statistical analyses will be conducted using SPSS for Windows (version 27.0). Statistical significance is defined as a two- sided *P*-value < 0.05. Baseline continuous variables will be expressed as mean ± SD (or median and interquartile range, as appropriate), and categorical variables as frequencies and percentages. Between-group comparisons of normally distributed continuous outcomes will use independent-samples *t*-test, while non-parametric continuous variables will be assessed with Mann-Whitney U test. Categorical data will be evaluated using chi-squared test or Fisher’s exact test. Group differences at weeks 16 and 24 will be tested via analysis of covariance (ANCOVA), adjusting for baseline values. Within-group changes over time will be examined with pair *t*-test for parametric data and Wilcoxon signed-rank test for non-parametric data. Based on the ITT, missing efficacy data will be imputed by last observation carried forward.

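### Last observation carried forward is fixed as the method for missing efficacy data: it shrinks a growing effect, and it can create or hide one if dropout differs by arm

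*Protocol article*

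**What the plan says.** Under Data processing and analysis, the protocol article fixes the rule for missing data: "missing efficacy data will be imputed by last observation carried forward". The same section names the between-group test that these values enter: "Group differences at weeks 16 and 24 will be tested via analysis of covariance (ANCOVA), adjusting for baseline values". The analysis set is given as follows: "All efficacy and safety endpoints will be analyzed under a modified intention-to-treat (ITT) framework". No other primary method for missing data is named.

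Three other places bear on the rule:

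- Sample size expects appreciable loss: "Allowing for an anticipated 20% dropout rate, the target total sample size was adjusted to 90 cases". At the planned 150 participants, 20% is 30 people.
- The abstract describes the patients as recovering: "Patients recovering from long COVID often endure a spectrum of neuropsychiatric symptoms".
- The abstract also provides for repeated measurement: "All outcomes will be assessed at baseline and then at 4 weeks intervals during both the treatment and post-treatment periods". Table 1 lists weeks 0, 4, 8, 12, 16, 20 and 24.

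Handling of withdraw and dropout keeps data collected before withdrawal and mentions no collection afterwards. People who leave would therefore have their later scores filled in.

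**The concern.** Last observation carried forward (LOCF) assumes that a score stops moving on the day the participant leaves. In this trial scores are expected to move, through treatment, natural recovery and repeated testing. Someone who leaves at week 4 is entered at week 16 with a week-4 score, usually worse than the one they would have reached. The filled-in value then counts in the ANCOVA as if it had been measured, so the standard error does not reflect that it is missing.

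Two consequences follow. If both arms lose people equally, a true effect that grows over time is diluted. If one arm loses more, that arm looks worse than it is. More loss on sham would then favour electroacupuncture, and more loss on active treatment would count against it. Unequal loss is plausible, because the arms differ in sensation (current strong enough to twitch muscle against non-penetrating needles without current) over 32 sessions. The article does not say that it is expected. Since the direction depends on which arm loses more people, LOCF cannot be defended as conservative.

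**Working it through.** **1. The plan's own figure.** For a two-sample t-test with d = 0.75, two-sided alpha 0.025 and power 0.80, n = 35.08, rounded up to 36 per arm. Allowing for dropout, 36 / (1 − 0.20) = 45 per arm, or 90 in total. Both figures in Sample size reproduce. LOCF does not enter that calculation.

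**2. Inputs.**
- From the article: 75 per arm (150 / 2); CBDI difference 3.96 and effect size 0.75, so SD = 3.96 / 0.75 = 5.28; dropout 20%; alpha 0.025 from Sample size (the analysis section states 0.05); visits every 4 weeks.
- Assumed: linear change to week 16; correlation 0.6 between any two visits; last observed visit spread evenly over weeks 0, 4, 8 and 12; dropout unrelated to outcome within arm; 0 to 8 points of improvement in the sham arm.

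**3. Expected size by arithmetic.** On average a dropout has reached (0 + 0.25 + 0.50 + 0.75) / 4 = 0.375 of the week-16 change, so LOCF loses 0.625 of it. For an arm with true improvement I and dropout d:

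LOCF improvement = I × (1 − 0.625 d)

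- Equal dropout, true difference 3.96: 3.96 × (1 − 0.625 × 0.20) = 3.96 × 0.875 = 3.465, which is 12.5% too small.
- No true effect, 10% v 30%: false difference = I × 0.625 × (0.30 − 0.10) = 0.125 × I, giving 0.25, 0.5 and 1.0 for I = 2, 4 and 8.
- True difference 3.96, sham improves 4, dropout 10% sham and 30% active: 7.96 × 0.8125 − 4 × 0.9375 = 6.47 − 3.75 = 2.72. Reversed: 7.96 × 0.9375 − 4 × 0.8125 = 7.46 − 3.25 = 4.21.

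**4. Simulation at week 16** (2,500 to 6,000 trials per scenario over two sets of runs; ANCOVA on LOCF values against ANCOVA on observed values only).

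| Scenario | LOCF estimate | LOCF rejection rate | Observed-data rejection rate |
|---|---|---|---|
| True 3.96, 20%/20%, sham improves 0 to 8 | 3.44 to 3.47 | 96% to 99.8% | 99.7% to 99.8% |
| Null, 20%/20%, both arms improve 0 to 8 | about 0 | 1.9% to 2.8% | 2.1% to 3.0% |
| Null, 10% v 30%, both improve 2 | 0.24 | 3.0% to 3.5% | 2.6% |
| Null, 10% v 30%, both improve 4 | 0.5 | 5.9% to 7.0% | 2.1% to 2.6% |
| Null, 10% v 30%, both improve 8 | 1.0 | 16% to 18% | 2.4% to 2.8% |
| Null, 15% v 25%, both improve 8 | 0.5 | 5% to 6% | 2.3% |

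The error rates can be checked by hand. With 8 points of improvement the mean LOCF standard error is 0.77, so the shift is 1.0 / 0.77 = 1.3 standard errors. Against a critical value of 2.26, that gives about 17%.

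With equal dropout and no improvement in the sham arm, the mean standard error is 0.69 for LOCF and 0.77 for the observed-data analysis. LOCF counts the filled-in values as information.

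**5. MMSE.** Implied SD = 2.82 / 0.76 = 3.71. With 1 or 2 points of improvement in both arms (assumed) and no true effect, 10% v 30% dropout gives a bias of 0.12 to 0.25 and an error rate of 3.1% to 4.1%. At 15% v 25% the bias is 0.06 to 0.14 and the error rate 2.3% to 3.1%.

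**6. Week 24**, 20%/20% dropout, true 3.96 at week 16. If the difference holds to week 24, LOCF gives 3.63 (true 3.96). If half of each arm's gain is lost after treatment, LOCF gives 2.00 to 2.02 (true 1.98).

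**The case against.** Most of the alarming figures rest on inputs that the documents do not contain. The article gives one dropout rate, not split by arm, and no trajectory. With equal dropout and no true effect, LOCF does not bias the test at all. The 17% error rate needs both a threefold imbalance in dropout and an 8-point fall in both arms. That fall is 8 / 5.28 = 1.5 SD, with sham included, in patients for whom eligibility sets no minimum CBDI score. For MMSE, which is capped at 30, the plausible bias is small. All of this stands, and it limits the size of the point.

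Four stronger readings are tempting, and the documents do not support them:

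- A reader might infer that LOCF necessarily biases both the week-16 and week-24 comparisons. It depends on trajectory and dropout pattern, and at week 24 the bias nearly vanishes if half the gain fades.
- A reader might infer a general loss of power. At the planned 3.96 points, power stays above 95% with equal dropout. A marked loss appears only with a smaller effect and large background improvement: for an assumed 2.5 points and 8 points of improvement it is about 67% against 82%, while with no background improvement both are about 82%.
- A reader might infer that the intermediate visits serve only as values to carry forward. The analysis section also plans within-group tests over time. What is missing is a stated between-group model that uses the visits jointly.
- A reader might take the simulation as proof that a mixed model performs better here. The comparator was ANCOVA on observed data, which is unbiased under the assumed dropout. Dropout related to outcome was not examined.

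It can also be said that an unseen analysis plan may add sensitivity analyses. That does not answer the point, because the article itself fixes LOCF as the method.

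**Conclusion.** The point holds as a conditional one. The article fixes LOCF for the values entering the week-16 and week-24 ANCOVA, with about a fifth of participants expected to leave and scores expected to change.

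On the article's own 20% figure, taken as equal in both arms and with linear change, the damage is a 12% to 13% understatement of a true CBDI difference (3.96 becomes about 3.5). The type I error stays near nominal and power stays high. If dropout differs by arm, LOCF can create or hide a difference: 0.125 of the shared improvement at 10% v 30%, and half of that at 15% v 25%. The 1.0-point bias and 17% error rate are a worst case, not a forecast.

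These sizes rest on the assumed trajectory, correlation 0.6 and dropout unrelated to outcome. The weakness of the rule does not: its error has no predictable direction, and the article gives no reason for choosing it.

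**What to change.** In Data processing and analysis, replace LOCF as the primary method by one of two options:

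- a mixed model for repeated measures on the scheduled visits, with baseline score, arm, visit and arm-by-visit terms and an unstructured covariance; or
- multiple imputation followed by the planned ANCOVA.

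Name the week-16 contrast as primary and week 24 as secondary. Add a delta-adjusted or reference-based sensitivity analysis for data not missing at random, and keep LOCF at most as supportive. Report dropout and its timing by arm.

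Before fixing the model, settle whether week 20 is assessed. Table 1 lists it, and the abstract's 4-weekly schedule implies it, but Outcomes measurement names only weeks 4, 8, 12 and 16 and the assessment two months after treatment.

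The cost is wording and a little programming. No new data are needed and the sample size (36 per arm, 90 with dropout, 150 planned) does not change. The change should be made before unblinding.

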### Data and Safety Monitoring Board (DSMB)

Data and Safety Monitoring Board will be established to oversee trial conduct and data integrity. The DSMB will convene at predetermined intervals to evaluate adherence to ethical and safety guidelines, verify the completeness and accuracy of collected data, and review overall study progress. It will also adjudicate adverse event reports and retain the authority to recommend suspension or early termination of the trial if participant safety or data validity is compromised.

### Adverse events

Throughout the trial, the treating acupuncturist will systematically document all AEs. Using a standardized reporting form, each episode’s timing, characteristics, intensity, and presumed cause will be captured. Before each session, the acupuncturist will also actively solicit any delayed reactions since the prior visit. Immediate on-site management will be provided for all events, and participants experiencing serious adverse events will be withdrawn from the study.

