### Randomization and blinding

Participants will be randomized in a 1:1 ratio to either the EAG or SCG. Those allocated to the active treatment arm will undergo standardized electroacupuncture sessions, while the control arm will receive an equivalent sham procedure. A computer-generated simple randomization sequence will be created prior to the study, without stratification or block assignment. The randomization procedure will be conducted by the research unit of the School of Chinese Medicine, Hong Kong Baptist University. Allocation codes will be placed in sequentially numbered, opaque, tamper-evident envelopes and stored in a locked cabinet, with sole key custody maintained by the Principal Investigator (PI). All participants, outcome assessors, statisticians, and all research staff involved in patient contact-except the acupuncturists delivering the treatments, will remain blinded to treatment assignment. To assess the success of blinding, the James Blinding Index will be used at the end of the study. Emergency unblinding is allowed if serious adverse events arise and immediate measures are required to ensure participant safety. Any request for emergency unblinding must be submitted to the PI by co-investigator. Appropriate medical interventions will be provided promptly, and the reasons for unblinding will be documented in detail, including the date and signature of the responsible investigator. The participant involved will be withdrawn from the study.

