#### Secondary outcome

Secondary endpoints include the score of ISI (56), BFI-T Form (57), and SF12 (58). All scales are assessed at baseline, at four-week intervals during the 16-week treatment phase (week 4, 8, 12, 16) and again at the 8-week post-treatment follow-up (Table 1). All adverse events will be prospectively recorded, with documentation of their intensity (mild, moderate or severe), duration, outcome, and potential relationship to the study.

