### Strengths and limitations of this study

This study is a rigorously designed, randomized, patient-assessor-blinded, sham-controlled trial, providing high-level evidence on the efficacy and safety of electroacupuncture for neuropsychiatric symptoms in long COVID patients.It employs validated outcome measures ensuring reliable assessment of cognitive, emotional, and sleep-related changes.The standardized electroacupuncture protocol, guided by expert consensus and evidence from systematic reviews, ensures consistent intervention across participants and centers.The study is limited to long COVID patients in Hong Kong, potentially reducing its generalizability to populations with different healthcare systems or cultural contexts.The sham acupuncture design, although validated, may not perfectly mimic the physiological and psychological effects of true acupuncture, potentially introducing bias.

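### First-line elicitation, grading and attribution of adverse events rest with the unblinded acupuncturist, and active questioning is described only at treatment sessions

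*Protocol article*

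**What the plan says.** The Adverse events section names the recorder and the period: for the whole of the trial, "the treating acupuncturist will systematically document all AEs". It names the content: "Using a standardized reporting form, each episode’s timing, characteristics, intensity, and presumed cause will be captured". It also describes one active question: "Before each session, the acupuncturist will also actively solicit any delayed reactions since the prior visit".

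The Randomization and blinding section lists participants, outcome assessors, statisticians and patient-contact staff, and then carves out one role: all "except the acupuncturists delivering the treatments, will remain blinded to treatment assignment".

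The Secondary outcome section repeats the recording duty without saying who rates: "All adverse events will be prospectively recorded, with documentation of their intensity (mild, moderate or severe), duration, outcome, and potential relationship to the study".

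The DSMB section adds a second layer: "It will also adjudicate adverse event reports and retain the authority to recommend suspension or early termination of the trial".

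Safety is more than routine monitoring here. Data processing and analysis puts safety endpoints under the same modified intention-to-treat framework as efficacy. The Discussion opens by naming safety among the things to be assessed rigorously. The Strengths and limitations section describes the trial as "providing high-level evidence on the efficacy and safety of electroacupuncture".

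Table 1 ticks the scales at baseline and at weeks 4, 8, 12, 16, 20 and 24. Its adverse event row has a single entry for the whole trial, saying that reports are made as needed.

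**The concern.** Asking, grading and attributing are the three steps at which knowledge of allocation can shape adverse event data. In the first instance the plan gives all three to the person who delivers the treatment. That person knows that the sham needles are non-invasive, placed off the acupoints and connected to inactive output ports (Interventions), and so has a clear expectation of which arm can cause harm. This could lead to less probing in the sham arm, or to readier attribution in the active arm. It could also work the other way, if the practitioner plays down events from a treatment they favour.

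What is at stake is the interpretation of the between-arm safety comparison. If elicitation differs by arm, events that were never recorded cannot be restored once data collection is over.

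The second part is timing. The one active question described is attached to treatment sessions, and these stop 8 weeks before the trial ends.

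**Working it through.** No figure in the article is in dispute, so the check is mainly a comparison of sections, followed by an illustration.

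**1. Who does what**

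| Step | Role named | Blinded? | Section |
|---|---|---|---|
| Asks about delayed reactions | Treating acupuncturist | No | Adverse events; Randomization and blinding |
| Records all events | Treating acupuncturist | No | same |
| Enters intensity and presumed cause | Treating acupuncturist, by the natural reading | No | Adverse events |
| Rates intensity and relationship | Not named | Not stated | Secondary outcome |
| Adjudicates reports | DSMB | Not stated | DSMB |
| Collects data in general | Data collector | Yes | Data management |

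The last row sits awkwardly with the first three: data collection is described as blinded, but the named collector of adverse events is not.

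**2. What adjudication can reach.** The DSMB works on reports. A report with a questionable grade or cause can be re-rated. An event that was not asked about, or not written down, produces no report. Adjudication can therefore act on rating bias but not on ascertainment bias.

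**3. Timing.** There are 32 sessions at 2 per week, which is 32/2 = 16 weeks. The trial lasts 24 weeks. The share of calendar time with no session-based question is (24 − 16)/24 = 8/24 = 33%. This is a share of time and not of event risk, which may well be concentrated in the treatment phase.

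**4. Illustration of unequal capture.** The article gives no adverse event rates or capture rates, so everything in this step except the arm size is an assumption. Take the same true risk p in both arms, n = 150/2 = 75 per arm, capture c₁ in the active arm and c₂ in sham, and a two-sided 5% test.

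- Recorded rates: p₁ = p·c₁ and p₂ = p·c₂. The apparent risk ratio is c₁/c₂ whatever p is.
- Probability of a significant excess in the active arm: Φ[(p₁ − p₂ − 1.96·SE₀)/SE₁], where SE₀ uses the pooled rate and SE₁ the separate rates.
- Worked case, p = 0.20 with capture 0.90 and 0.70: p₁ = 0.18 and p₂ = 0.14. SE₁ = √(0.18·0.82/75 + 0.14·0.86/75) = 0.0598, and SE₀ is nearly the same. The probability is about Φ(0.04/0.0598 − 1.96) = Φ(−1.29) = 9.8%.

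| Capture, active vs sham | Apparent risk ratio | Probability of a false significant excess, p from 10% to 40% |
|---|---|---|
| 95% vs 80% | 1.19 | 5% to 12% |
| 90% vs 70% | 1.29 | 7% to 18% |
| 90% vs 50% | 1.80 | 16% to 59% |

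With equal capture the probability in that one direction would be 2.5%, half of the two-sided 5%. If capture were unequal in the opposite direction, the table would apply with the arms exchanged.

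**The case against.** Several stronger readings are tempting, and the document does not support them.

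- *That safety is judged only by the unblinded acupuncturist.* The DSMB adjudicates reports, and nothing shows that the acupuncturist's rating is final. The point concerns the first line.
- *That events are recorded only before sessions.* Recording is said to run throughout the trial, and the pre-session question comes in addition.
- *That Table 1 treats follow-up differently.* Its as-needed entry covers the whole adverse event row, treatment phase included.
- *That follow-up has no active ascertainment, so delayed events are missed.* The text supports only that none is described. Visits exist at weeks 20 and 24, a hotline and email address run throughout, and the full protocol is not shown. A visit-level question is the kind of detail that an article may leave out.
- *That the plan breaks a promise of blinded safety assessment.* No section makes that promise. The trial is called patient-assessor-blinded, and safety is a separate aim.

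There are also real mitigations. Participants are blinded, and they are the source of what is solicited. The form is standardized. The acupuncturist is the natural recorder of immediate reactions to needling.

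These arguments limit the point but do not remove it. The assignment of recording to the acupuncturist is a stated choice and not an omission, so condensation into an article does not explain it. A blinded participant does not prevent the questioner from probing differently by arm, and a standardized form does not blind the person completing it.

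**Conclusion.** The concern holds in a limited form. First-line elicitation, intensity grading and causal attribution are given to the one role exempt from blinding, in a trial that analyses safety and claims to provide evidence on it. DSMB review does not remove the resulting ascertainment risk. Active questioning is described only at sessions, which leaves 8 of 24 weeks without any described.

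Neither the direction nor the size of any bias can be derived from the documents. The capture table shows only how much could follow from assumed differences: at 95% vs 80% the distortion is modest, and at 90% vs 50% it is large. A reader should not infer that the safety results will be biased. The inference is that, under this arrangement, a difference or a lack of one could not be read with confidence. No efficacy outcome depends on the point. It is a worthwhile, inexpensive improvement to the safety comparison and not a flaw in the trial's main question.

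**What to change.** 1. Keep the acupuncturist recording immediate procedural events.
2. Add a fixed adverse event item, identical in both arms and completed by the participant, at existing visits 2 to 7, which include weeks 20 and 24. It should be completed after the MMSE and not shown to the MMSE assessor. Reports of bleeding, bruising or twitching could reveal allocation, and the MMSE is a primary outcome, so that assessor should not be the one who asks.
3. Have intensity and relatedness rated by a blinded co-investigator or by the DSMB, from forms without allocation, and state whether the DSMB is blinded when it adjudicates.
4. Name these scheduled, blind-rated reports as the main between-arm safety comparison, with the acupuncturist's records reported alongside.

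The cost is one short form at visits that already take place, modest rating work for existing roles, and two event sources to reconcile. A small risk remains that a described local reaction hints at allocation to the rater. No new visits are needed.

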**Withdrawal criteria**	
• Confirmation of pregnancy during the trial.**** • Discovery of a disease that may affect the trial.**** • Problems with the medical or trial procedures.**** • Other reasons determined by the research team.	

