### Handling of withdraw and dropout

Participants who meet withdrawal criteria or voluntarily withdraw from the study will have their reasons documented whenever possible. Data collected before withdrawal will be retained for analysis under the intention-to-treat principle unless consent is specifically withdrawn for data usage. Efforts will be made to minimize dropout through proactive follow-ups, flexible scheduling, and continuous communication via the designated email and hotline. Adverse events (AEs) or concerns will be addressed promptly, and any serious issues will be reported to the PI and the ethics committee. Withdrawals and dropouts will be transparently reported in the final study results to ensure data integrity and scientific rigor.

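### Withdrawal from the study after a serious adverse event or unblinding leaves later outcomes to be imputed, so the intention-to-treat comparison is not assured

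*Protocol article*

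**What the plan says.** Three routes lead out of the trial after randomization.

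- **Serious adverse event** (Adverse events): "participants experiencing serious adverse events will be withdrawn from the study".
- **Emergency unblinding** (Randomization and blinding): "The participant involved will be withdrawn from the study".
- **Open criteria** (Table 2, Withdrawal criteria): among others, "Discovery of a disease that may affect the trial" and "Other reasons determined by the research team".

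Handling of withdraw and dropout then says what happens to the data: "Data collected before withdrawal will be retained for analysis under the intention-to-treat principle unless consent is specifically withdrawn for data usage".

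Data processing and analysis says: "All efficacy and safety endpoints will be analyzed under a modified intention-to-treat (ITT) framework". The same section ends: "Based on the ITT, missing efficacy data will be imputed by last observation carried forward". It tests group differences at weeks 16 and 24 by ANCOVA adjusted for baseline.

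**The concern.** The first two rules are worded as leaving the study, not as stopping the sessions. The article nowhere separates the two. If leaving the study also ends the questionnaires, the plan itself creates missing outcomes in participants who could still have been assessed.

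Such gaps are unlikely to be random. A serious event may be related to treatment, and an unblinding request follows such an event. Both can be unequally frequent in the two arms. Carry-forward then replaces each missing week 16 and week 24 value with one recorded before the event. The between-group estimate depends on how far that earlier value lies from the unobserved one, and on how unequal the withdrawals are. Recruiting more participants does not remove this kind of error.

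The analysis labels do not settle the matter. The data-handling section invokes intention-to-treat, the analysis section places all endpoints under a modified version, and its last sentence returns to the unmodified term.

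**Working it through.** **1. The plan's own figure.** The Sample size section gives an effect size of 0.75 for BDI, two-sided alpha 0.025, power 0.80 and 1:1 allocation. A two-sample t-test calculation with the noncentral t distribution gives 36 per arm (power 0.811 at 36, 0.799 at 35). For 20% dropout, 72 / (1 − 0.20) = 90. Both stated figures reproduce.

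**2. Power is not the issue.** With 150 recruited there are 75 per arm, and power at the planned effect is 0.990. With 20% lost, 75 × 0.80 = 60 per arm remain and power is 0.966. What is at stake is bias.

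**3. What is lost per participant.** Table 1 schedules six post-baseline assessments (weeks 4, 8, 12, 16, 20 and 24). Withdrawal before week 4 loses all six, and later withdrawal loses fewer. Any withdrawal before week 16 loses both ANCOVA time points.

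**4. What the sections say together.**

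| Question | Where | Answer in the text |
|---|---|---|
| What does the participant leave? | Adverse events; Randomization and blinding | The study |
| Which data are said to be kept? | Handling of withdraw and dropout | Those collected before withdrawal |
| How are missing efficacy values filled? | Data processing and analysis | Last observation carried forward |
| Do assessments continue after withdrawal? | Nowhere | Not stated |

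The natural reading is that assessment stops and carry-forward supplies the rest.

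**5. Size, by assumption only.** The article gives no rate of serious events, unblinding or discretionary withdrawal. Let w be the arm difference in the proportion withdrawn early, and g the average gap between the carried-forward value and the true later value. The group difference shifts by about w × g.

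- In CBDI points, assume w = 0.05 and g = 8. The shift is 0.05 × 8 = 0.4 point. Against the planned difference of 3.96 this is 0.4 / 3.96 = 10%.
- In SD units, the SD implied by the plan is 3.96 / 0.75 = 5.28, so 0.4 / 5.28 is about 0.08 SD.
- Over a range in SD units, w = 0.02 with g = 0.5 gives 0.01 SD, and w = 0.10 with g = 1 gives 0.10 SD.

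The 0.4 point is an upper bound for these inputs, because it takes the whole 8-point improvement as unobserved. With 75 per arm, w = 0.05 means 0.05 × 75 = 3.75, about four withdrawals in one arm against none in the other. The sign is not fixed. Carry-forward understates an arm whose withdrawn participants would have improved, and flatters it if they would have worsened.

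**The case against.** The strongest reply is that the plan keeps withdrawn participants in the comparison. "Data collected before withdrawal will be retained for analysis under the intention-to-treat principle" is explicit, and carry-forward gives them a week 16 and week 24 value. This stands. A reader might infer that they are dropped from the analysis and that intention-to-treat is therefore not delivered, but no sentence excludes anyone.

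Three other stronger readings also fail.

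- **Safety follow-up ends with withdrawal.** The article does not say so. Secondary outcome requires the duration and outcome of every adverse event to be recorded, which presupposes some follow-up. The Data and Safety Monitoring Board also adjudicates event reports.
- **The modified intention-to-treat set is undefined.** The definition may stand in a full protocol or analysis plan that is not shown, so its absence is no error. Only the difference in labels is visible in this text.
- **Unblinded acupuncturists decide who leaves.** They know the allocation and document the events. The discretion is given to the research team, however, and unblinding requests go from a co-investigator to the principal investigator.

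It is also fair to say that the end of outcome assessment is inferred from the wording and not stated outright. The inference is natural, since the only data mentioned are those collected before withdrawal, but one clarifying sentence could dispel it.

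Finally, the 0.4 point rests wholly on assumed inputs. The assumed imbalance is one-sided, and 8 points is about twice the planned difference. It shows scale and is no forecast.

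**Conclusion.** The concern holds in a limited form. Study withdrawal is mandatory after a serious adverse event or emergency unblinding and discretionary for other reasons. No provision for later outcome assessment is stated, and the gap is filled by carry-forward. Week 16 and week 24 outcomes would therefore be imputed where they could have been observed, after events that may differ by arm. The intention-to-treat comparison is not assured, and the two labels need reconciling.

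The likely effect is small: at most 0.4 CBDI point (about 0.08 SD) under the assumed 5-percentage-point imbalance and 8-point unobserved improvement, and less if such events are rare. The case for acting is that outcomes not collected cannot be recovered later and that the remedy is cheap. The conclusion assumes that withdrawal from the study means what it ordinarily means. It would lapse if the full protocol already provides for continued assessment.

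**What to change.** Leave the treatment-stopping and unblinding rules as they are; this point takes no position on them. Make two changes to the wording.

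1. In Randomization and blinding, the withdrawal criteria of Table 2, Handling of withdraw and dropout, and Adverse events, state that stopping sessions or being unblinded does not by itself end study participation. State that scheduled outcome assessments and adverse-event follow-up continue to week 24 unless the participant withdraws consent for follow-up.
2. Reconcile Handling of withdraw and dropout with Data processing and analysis, so that the primary efficacy analysis includes all randomized participants as allocated, under one consistent label.

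The cost is protocol wording and some extra follow-up contacts, at visits already in Table 1.
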